### Intervention preparation

#### NIPP and NIPP+ intervention training/session modules

Through the 12-week intervention period, NIPP volunteers will conduct sessions that will cover the following elements to the circle participants:
Promotion of food hygiene practices;How to keep the water source safe by identifying the small doable actions that will be used as a metric of assessment such as:
Using different containers for transportation and storage of household potable water;Regular cleaning of storage and transportation water containers;Handwashing and use of tippy taps to conserve water;Separate animals from humans within the household to reduce fecal contamination of water;Use of simple water purification methods (e.g., boiling, solar disinfection, etc.) (NIPP+ only);Demonstrate how simple water quality kits can identify contamination (NIPP+ only); andDemonstrate simple methods (at the household and community levels) to support improving the quality of water (Hamoudi, 2012) (NIPP+ only).

To reinforce impact and empower the women and men in the NIPP circles, we will encourage them to maintain a record of their results on forms adapted for the general literacy levels of the target populations. All materials will be tested and contextualized to the local situation and translated into Acholi.

Agricultural demonstration plots will be planted and used to train the NIPP+ volunteers on GAP. The harvest from the demonstration plots will be bagged in both hermetic and non-hermetic storage bags to use for demonstration at the NIPP+ volunteer training. We anticipate providing hermetic bags, seed packs, and fertilizer samples to the NIPP+ volunteers who will demonstrate the use of these inputs within their own circles. Volunteers will be encouraged to store their maize from the harvest of the demonstration plots in hermetic bags to show the circle participants the benefits of using the bag.

In addition, inputs provided to the NIPP+ volunteers to improve the household’s WASH environment will include Aquagenx CBT H_2_S water testing kits (CBT kit; Aquagenx, Chapel Hill, NC) for demonstration purposes and 5-L jerry cans. NIPP+ volunteers will be trained to use the water quality kits and then asked to demonstrate the kit to their NIPP+ participants along with clear doable actions to improve WASH-specific behaviors. To ensure that NIPP+ volunteers have access to seeds, hygrometers, hermetic bags, and water quality testing kits (so that participants might buy them at low cost), participants and volunteers will be linked to agro-dealers who sell seeds of improved maize varieties, hermetic bags, and moisture meters and to vendors for water quality kits. Though we will aim to make these available for low cost, it may be that the kits will have to be provided (at least one kit) per household to ensure households are able to try out the kits to better understand their value. For both NIPP and NIPP+, pilot high-energy nutrient-rich recipes will be developed through market surveys and observation visits to local homesteads to determine the full range of foods available, accessible, and affordable and then use the results of the market surveys to pilot a variety of high-energy nutrient-rich recipes.

The identified volunteers in both NIPP and NIPP+ groups will undergo a rigorous training in two phases — a preliminary phase whereby all volunteers assume the role of the circle participants and are trained by project staff in collaboration with relevant district government staff and a second phase whereby the volunteers become the circle lead and practice leading sessions themselves.

#### COVID-19 reconfiguration

To accommodate safety measures put in place to mitigate the potential spread of COVID-19, both the NIPP and NIPP+ modules were altered to add a session about COVID-19 which included practice on how to properly wear a mask, sensitization about what COVID-19 is, symptoms, and how it is spread between individuals, and additional emphasis on the importance of handwashing with soap or ash to prevent the spread of disease. In addition, each session was amended to begin with a demonstration of proper facemask protocol so that all participants were wearing facemasks correctly for the duration of the program. These additions expanded the standard program design from 12 to 16 weeks.

### Data collection

Data will be collected on all participants (*n* = 900 in 60 clusters) at the start of the program (baseline), at 4 months after baseline (endline), and at the sustainability measurement (12 months after the end of the intervention) (Fig. 1) by enumerators trained in the proper anthropometric, survey, water collection, and maize collection methods. We will also collect data on a subset of households 2 months and 6 months after the completion of the intervention (“Monitoring Activity” in Fig. 1). We will collect maize samples a few months after endline and a few months after sustainability, which corresponds approximately to September in the intervention year and September in the follow-up year following each year’s harvest. Finally, samples using an in-development smartphone technology for assessing aflatoxin levels in capillary blood will be collected in parallel with the maize aflatoxin data collection (see the “Tools and data collection” section for more detail).

**Fig. 1 Fig1:**
[figure not shown]
Intervention timeline and key milestones

To assess the potential for scale and identify best practices, qualitative assessments will be conducted at the end of the intervention (endline), at follow-up 2 months and 6 months, and as part of the sustainability assessment (12 months after the end of the intervention). The format used for the qualitative assessment will be structured key informant interviews for program staff and NIPP and NIPP+ volunteers along with focus group discussions with NIPP circle participants. The planned data collection for qualitative assessments are:
Endline: Structured key informant interviews with program staff and NIPP and NIPP+ volunteers facilitating the circles. The focus will be discussing difficulties they faced during planning and implementation, how they worked through those difficulties, the relative success of different approaches (both NIPP and NIPP+), and lessons learned from that process.Endline-sustainability: Focus group discussions of 30 female and 30 male participants will be interviewed to understand what motivated those who decided to invest in the innovations, or to adopt promoted practices, as well as what discouraged other participants from doing the same.Two- and 6-month follow-up and sustainability: Focus group discussions with the same 30 female and 30 male participants to assess any shift in the various practices and better understand factors that encouraged or discouraged them in maintaining the innovations or practices, as well as their perceived costs and benefits.

### Sample size calculation and sampling strategy

To detect meaningful differences in the change in the primary outcome measures across the three arms with a power of 0.80, a significance level of 0.05, and an intra-class correlation of 0.05, each treatment arm will require 17 clusters with 15 households (with children under the age of 2) in each cluster (Table 2). We used secondary data on all outcome measures (except total coliform) from Northern Uganda and collected as part of the Feed the Future Innovation Lab for Nutrition Uganda Birth Cohort Study [24]. We aim to follow the same households throughout the duration of the study. Thus, the sample size is adjusted for 20% attrition. This increase will come from additional clusters and not households (to keep the integrity of the NIPP 15 households/circle programmatic design). The sample will include 20 clusters per arm for a total of 60 clusters and 15 households per cluster with an overall household sample size of 900. Based on the results of cluster randomization, trained study personnel will approach households that meet the study’s inclusion criteria in the parishes selected for the study. They will approach eligible households and seek consent until a total of 15 households agree thus forming a cluster. The sampling at the household level is purposeful. A random subsample of households will be taken at 2 months and interviewed again at 6 months post-intervention. This sample size is a fixed sample of 82 households per intervention arm.

**Table 2 Tab2:** Sample size calculation for quantitative evaluation

Category	Mean	*SD*	ICC^a^	Effect size (Cohn’s)	Sample size/treatment arm	Total sample size
*E. coli*	31.56	45.14	0.05	0.67	120 (20 clusters*5 hh per cluster + 20% for attrition)	≈ 360
Aflatoxin	20	43.6	0.05	0.34	306 (17 clusters*15 hh per cluster + 20% for attrition)	≈ 900

^a^The ICC calculated for aflatoxin for mothers was close to 0 but came from a small sample size. Thus, we have decided to overestimate the ICC to 0.05

The criteria for community selection include food security, water access, security, community cohesion, and geographic proximity to one another to decrease the probability of contamination between the arms (GOAL 2018). These criteria will be applied in the selection of all 60 clusters (intervention and control). Tufts will utilize block randomization to randomly assign clusters to 1 of 3 treatment groups and will only share the list of clusters by treatment arm (not how they were assigned). A total of 60 clusters (a “cluster” is a group of 3 NIPP circles and may be at either parish or village level, dependent on population density — see Table 1 for subcounty-level estimates of cluster representation) will be randomly assigned to the three groups (20 clusters per group). We will randomize at the parish level by assigning random numbers to each parish, ranking the parishes by random assignment, and assigning to a treatment group after the ranking is complete such that group 1 is randomized to Control, group 2 to NIPP, and group 3 to NIPP+. The households will be selected purposefully after clusters have been randomized to specific arms. Each cluster in groups 1 and 2 will have one male, one female, and one community NIPP circle. Each circle will include 10–15 individuals with the cluster serving as the primary unit of analysis. As this is a community-based intervention cluster-randomized trial, it is impossible to conceal from participants which treatment arm they have been randomized to and which intervention they have the opportunity to consent to being a part of.

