The specific models run will depend on the distribution of our key outcome variables. Most of our variables are continuous and therefore we will use either an ordinary least squares, Poisson, or negative binomial regression (depending on the distribution of the variable) to compare across the three treatment arms. For binary variables (such as whether the household reported using improved seeds), we will use a logit model. All analysis will control for the complex survey design. For each key outcome variable, we will run a crude model (meaning only looking at the relationship between the outcome variable and intervention) and an adjusted model (controlling for key household and child demographics such as gender, age, education, and household size). A comprehensive research uptake strategy will be developed alongside stakeholders in Uganda.

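### The E. coli row of Table 2 does not follow from its own inputs, and neither tabled effect size is converted into the reduction it implies

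*Protocol article*

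**What the plan says.** The section on sample size and sampling strategy sets the calculation "with a power of 0.80, a significance level of 0.05, and an intra-class correlation of 0.05", and says that the target is a meaningful difference between arms in the change of the primary outcomes. Sidedness, a pre–post correlation and the contrast being powered are not given.

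Table 2 has two rows, each listing mean, SD, ICC and effect size:

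- E. coli: "31.56 45.14 0.05 0.67", with a sample per arm of "120 (20 clusters*5 hh per cluster + 20% for attrition").
- Aflatoxin: "20 43.6 0.05 0.34", with a sample per arm of "306 (17 clusters*15 hh per cluster + 20% for attrition").

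The table footnote explains the ICC: "The ICC calculated for aflatoxin for mothers was close to 0 but came from a small sample size", so 0.05 was used instead. The final design is 20 clusters of 15 households per arm. The water-sampling section takes 6 household samples in each of 60 clusters, 360 in all, which agrees with the E. coli total in Table 2.

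For the analysis, the section on statistical methods says that "we will use either an ordinary least squares, Poisson, or negative binomial regression (depending on the distribution of the variable").

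**The concern.** Two things in Table 2 need attention.

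First, an effect of 0.67 is large for a cluster trial with a small ICC and 5 households per cluster, and should need far fewer than 100 households per arm. Either the effect size, the sample or an unstated assumption is wrong.

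Second, both SDs exceed their means. A standardised effect that looks moderate (0.67) or small (0.34) can then be a very large share of the mean. Because the table does not convert the effects, a reader cannot see this. A null result on water or grain contamination would be read as coming from a trial with 80% power against meaningful differences, when a halving of contamination could be missed about as often as it is found for aflatoxin, and about four times in ten for E. coli.

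**Working it through.** **Inputs.** Power 0.80, alpha 0.05, ICC 0.05, and the means, SDs and effect sizes are all from the sample size section and Table 2. Two-sided testing of two arms is assumed.

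**Formula.** n per arm = 2 × (1.96 + 0.8416)² / d² × [1 + (m − 1) × ICC] = 15.698 / d² × design effect, with m households per cluster. As a check, power is also taken from a noncentral t with 2(k − 1) degrees of freedom for k clusters per arm.

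**Aflatoxin row.** d = 0.34, m = 15, design effect 1 + 14 × 0.05 = 1.70.
- 15.698 / 0.1156 = 135.8; × 1.70 = 231; / 15 = 15.4, so 16 clusters by the normal approximation.
- With the t distribution, 16 clusters give power 0.789 and 17 give 0.815.
- 17 × 15 = 255; × 1.2 = 306. The row reproduces.

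**E. coli row.** d = 0.67, m = 5, design effect 1 + 4 × 0.05 = 1.20.
- 15.698 / 0.4489 = 35.0; × 1.20 = 42; / 5 = 8.4, so 9 clusters by the normal approximation.
- With the t distribution, 9 clusters give 0.777 and 10 give 0.824. The requirement is therefore 42 to 50 households per arm before attrition, against a stated 20 × 5 = 100.
- 42 with attrition is 51 (× 1.2) or 53 (/ 0.8), against a stated 120.

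**Could another assumption give 100?** Before attrition, for E. coli:
- one-sided alpha: 33;
- 90% power: 56;
- alpha 0.0167 for three contrasts: 56, or 72 with 90% power;
- alpha 0.01 with 90% power: 80 (96 to 100 after attrition), which contradicts the stated alpha and power and gives 438 for aflatoxin, not 255;
- change score with zero pre–post correlation: 84 (101 after × 1.2), which would count attrition twice and gives 462 for aflatoxin, not 255;
- solving for the ICC: (100 / 34.97 − 1) / 4 = 0.46, not 0.05.

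None fits both rows.

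**What 20 × 5 does deliver.** Effective n = 100 / 1.20 = 83.3 per arm. Power at 0.67: 0.67 × √(83.3 / 2) − 1.96 = 2.365, so 0.991 (0.988 with t). Detectable d at 80% power: 2.8016 × √(2 / 83.3) = 0.434 (0.445 with t).

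**Effects in natural units.**
- E. coli: 0.67 × 45.14 = 30.2; 30.2 / 31.56 = 96%.
- Aflatoxin: 0.34 × 43.6 = 14.8; 14.8 / 20 = 74%.

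**Reductions detectable with 80% power, raw scale** (ranges run from normal to t; percentage = d × SD / mean):

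| Outcome, analysed sample per arm | Detectable d | Fall in units | Fall, % of mean | Power for assumed 50% fall |
|---|---|---|---|---|
| E. coli, 20 × 5 | 0.434–0.445 | 19.6–20.1 | 62–64 | 0.62–0.59 |
| E. coli, 20 × 6 (no loss) | 0.404–0.415 | 18.3–18.7 | 58–59 | 0.68–0.66 |
| Aflatoxin, 17 × 15 | 0.323–0.334 | 14.1–14.5 | 71–73 | 0.51–0.49 |
| Aflatoxin, 20 × 12 (20% lost) | 0.318–0.327 | 13.9–14.2 | 69–71 | 0.52–0.50 |
| Aflatoxin, 20 × 15 (no loss) | 0.298–0.306 | 13.0–13.3 | 65–67 | 0.58–0.56 |

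The 50% fall is an illustration, equal to d = 15.78 / 45.14 = 0.350 and 10 / 43.6 = 0.229. For an assumed 30% fall, power is about 0.26–0.27 for E. coli (20 × 5) and 0.21–0.25 for aflatoxin.

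**The case against.** The best defence is that nothing here shows an underpowered trial. The E. coli error is conservative: the sample is more than twice what its stated effect needs. The aflatoxin sample is right for its stated effect. Both points stand, so the inconsistency in the E. coli row is not evidence of low power.

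A reader might go further and infer that the trial can detect only the near-elimination of contamination. It cannot be put that way: 96% is what the tabled effect implies, while the planned sample reaches 80% power at about 62–64%. Nor do the documents show that large falls are unrealistic. They give no expected reduction, and the NIPP+ package includes hermetic storage and water disinfection. The 50% and 30% cases are therefore illustrations only.

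The percentages also assume that the tabled mean is the control level and the tabled SD that of the analysed quantity. The text powers a difference in change, and Table 2 defines neither. Baseline adjustment could lower the detectable fall for E. coli, which is measured at baseline. It cannot do so for grain aflatoxin, which Table 3 lists only at endline and sustainability.

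On skewness, the analysis section allows count models as well as least squares, so raw-scale power may not be the power of the final analysis. A log-scale analysis would be reasonable, but it changes the estimand, and any gain claimed for it rests on an assumed distribution and ICC on that scale. It is an option, not a correction the documents require.

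Finally, a reader might take the footnote to mean that the aflatoxin mean and SD came from mothers. It ties only the ICC to mothers; the source of the other two figures is unclear.

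**Conclusion.** The concern holds as a fault in the sample size table. The E. coli row is internally inconsistent by a factor of about two (42–50 households per arm needed for d = 0.67, 100 stated), and no single alternative assumption that was tried explains both rows. The tabled effects amount to about 96% and 74% of the tabled means, and this is not disclosed. The planned sample has 80% power for falls of about 62–64% in E. coli and 65–73% in aflatoxin, and power of about 0.6 and 0.5 for a halving (up to 0.68 and 0.58 if no household is lost).

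These figures rest on a two-sided test, two-arm comparisons, the raw scale, an ICC of 0.05, and the tabled means and SDs describing the control level and the analysed quantity. They do not show that the stated power is false for the stated effects, and they do not call for a different sample.

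**What to change.** Keep the sample. In Table 2 and its text:

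1. Restate the E. coli effect size as about 0.43–0.45 for 20 × 5, or give the assumption that turns 0.67 into 100 per arm. Cutting the water sample to 10 × 5 to match 0.67 would also make the row consistent, but it would halve the samples and raise the detectable fall, so it is not advised.
2. Beside each effect size, give the absolute and percentage reduction it implies, and say whether the mean is a control-arm level and the SD that of a single measurement or a change.
3. State the reductions detectable at 80% power with the actual sample, so that a null result is not read as 80% power against smaller falls.
4. State whether the aflatoxin mean and SD come from mothers or from grain.

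A log-scale or log-link analysis may be chosen for these skewed outcomes. If it is, the detectable reductions should be given on that scale too.

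The cost is a revised table and a few sentences. No household, sample or visit changes.

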#### Statistical methods for assessing impact

For the analysis, we will use an intent-to-treat (ITT) approach using the initial randomization of the treatment arms. While we know that there could be some contamination across groups or non-adherence, we will plan for the clusters to be sufficiently far apart that this should limit any bias related to self-selection captured via retention or adherence. Using ITT will allow us to determine the overall impact of having the NIPP vs. NIPP+ vs. control in your community, thus better mimicking real-world program implementation and impact. Each survey question will have the option of “Refused to Answer” or “Don’t Know” and will eventually be transformed into missing variables. Prior to that transformation, we will use the proportion of RA or DK responses to understand the sensitivity of the question itself. We will use the standard rule where if fewer than 5% of your observations are missing, the variable will remain in the analysis. If the 5% or more of observations are missing, we will not use the variable to avoid drawing inaccurate inferences. We will not impute missing data.

For the analysis, we will take advantage of the panel to run mixed effects models, allowing us to determine the role of time-variant and invariant individual household, and community characteristics, as well as measures of exposure and integration on key outcome indicators (Table 1 above). In addition, we will use a difference-in-difference analysis (baseline/endline, baseline/sustainability, endline/sustainability) to triangulate findings. To complement these models, the analysis will also leverage exploratory analysis to identify cross-cutting or underlying correlations using principal component analysis. For all of the analysis, we will control for a host of individual-, household-, and community-level characteristics.

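### The cluster-selection criterion asks for geographic proximity to reduce contamination, while the analysis section relies on clusters being far apart; the two statements must be reconciled

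*Protocol article*

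**What the plan says.** Under 'Sample size calculation and sampling strategy', the protocol article lists its criteria for selecting communities: food security, water access, security, community cohesion, and "geographic proximity to one another to decrease the probability of contamination between the arms". It then fixes the scope: "These criteria will be applied in the selection of all 60 clusters (intervention and control"). Assignment to arms is described after this. The same paragraph speaks of randomly assigning 60 clusters to three groups and also says "We will randomize at the parish level by assigning random numbers to each parish".

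Under 'Statistical methods for assessing impact', the article states that "we will use an intent-to-treat (ITT) approach using the initial randomization of the treatment arms". It concedes the risk ("While we know that there could be some contamination across groups or non-adherence") and gives its safeguard in the same sentence: "we will plan for the clusters to be sufficiently far apart that this should limit any bias".

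**The concern.** Both sections aim to limit contamination between arms, but one names closeness as the means and the other names distance. A team that followed the selection criterion as worded would prefer clusters near one another before any arm is known, and some of those neighbours would then fall into different arms.

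The protocol itself describes routes by which an intervention could reach a neighbouring cluster:

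- community water sources, where *E. coli* at the source is listed as a primary outcome;
- vendors and agro-dealers who sell bags, seed and test kits;
- community circles made up of local leaders.

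Spillover into control, or from NIPP+ into NIPP, would generally pull those contrasts toward no difference. An intent-to-treat analysis preserves the randomized comparison but does not undo that dilution. The sample size calculation uses the full planned effect, with no allowance for spillover.

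**Working it through.** **1. The two statements side by side.** The selection criterion asks for proximity of the communities to one another and gives less contamination between arms as the purpose. The analysis section plans for clusters far enough apart to limit bias. Could proximity be meant only within a cluster or within an arm? The text does not support this: the criteria cover all 60 clusters, intervention and control, and selection precedes assignment. The words therefore apply to clusters that may end up in different arms.

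**2. What parish-level randomization does.** Table 1 lists 10 subcounties with 4 + 7 + 6 + 6 + 8 + 5 + 7 + 3 + 4 + 6 = 56 parishes. Sixty clusters in 56 parishes is 60/56 = 1.07 per parish, so at least one parish must hold more than one cluster. The abstract speaks of 5 subcounties. Any five in Table 1 hold between 22 and 34 parishes, which gives 60/34 = 1.8 to 60/22 = 2.7 clusters per parish.

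These counts do not by themselves show contact between arms. If the parish is the unit of assignment, clusters in one parish share an arm and only contact across parish borders remains. If the cluster is the unit, clusters in one parish can fall in different arms. The text supports either reading.

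**3. The planned sample size, reproduced.** Inputs from the sampling section: "with a power of 0.80, a significance level of 0.05, and an intra-class correlation of 0.05". Table 2 gives d = 0.34 for aflatoxin and 15 households per cluster. A two-sided test is assumed.

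- Per arm without clustering: 2 × (1.960 + 0.842)² / 0.34² = 135.8, rounded up to 136.
- Design effect: 1 + 14 × 0.05 = 1.70, so 136 × 1.70 = 231.2 households, or 231.2/15 = 15.4 clusters.
- Adding one cluster for a cluster-level t-test: 16.4, rounded up to 17. This matches "each treatment arm will require 17 clusters with 15 households".
- 17 × 15 × 1.2 = 306, as in Table 2. The trial then uses 20 clusters per arm.

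The figure reproduces, and no step in it allows for spillover.

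**4. Illustration of dilution.** The documents give no spillover rate, so a share c is assumed and the effect becomes 0.34 × (1 − c). With 20% attrition, 15 × 0.8 = 12 households remain per cluster. The design effect is 1 + 11 × 0.05 = 1.55, and the effective sample is 240/1.55 = 154.8 per arm. The noncentrality is d × √(154.8/2), tested two-sided at 0.05 on 2 × 20 − 2 = 38 degrees of freedom.

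| Assumed c | Diluted d | Noncentrality | Power (t, 38 df) | Power (normal) |
|---|---|---|---|---|
| 0 | 0.340 | 2.99 | 0.83 | 0.85 |
| 10% | 0.306 | 2.69 | 0.75 | 0.77 |
| 20% | 0.272 | 2.39 | 0.65 | 0.67 |
| 30% | 0.238 | 2.09 | 0.53 | 0.55 |

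These figures show how sensitive the design is to dilution in general. They do not estimate what the wording of the criterion would cause.

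**The case against.** The strongest reply is that this is a matter of wording. The listed criteria are names of dimensions without a direction, and the only direction attached to proximity is its purpose, to lower contamination, which agrees with the analysis section. The criterion also cites a programme source that is not at hand and may define it. It is fair that a drafting slip is possible. But the phrase is a criterion for choosing clusters, and its ordinary meaning is closeness, so the text still needs correcting.

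A second reply is that parish-level randomization already protects against mixing within a parish. This largely stands, provided the parish really is the unit of assignment. It leaves contact across parish borders, and the same paragraph also speaks of assigning clusters.

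A third reply is that the power losses rest on an invented spillover share, and that a control household hearing messages would not gain the full NIPP+ package of training, vendor links and at least one free bag. This stands: the figures are illustration only.

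Two stronger readings are tempting and should be resisted. A reader might infer that contamination between arms is unavoidable because clusters must share parishes. That does not follow if parishes are assigned whole. A reader might also infer that distance is the trial's only protection, or that the intent-to-treat analysis is invalid. Distance is the safeguard named in the analysis section, but parish-level assignment may act as another. The article accepts some contamination and does not claim that intent-to-treat removes it. Nor is the absence of a stated buffer distance a fault, since a journal article may leave that to the full protocol.

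**Conclusion.** The contradiction holds. Taken literally, the selection criterion favours neighbouring clusters and works against the separation that the analysis section relies on. This is more than clerical, because it concerns how all 60 clusters are chosen, but it does not show that the trial has been contaminated. Any increase in spillover is an inference from the wording: the documents give neither distances nor a rate, so the size of any dilution is unknown. Under an assumed dilution of 10–30%, a two-sided test and 20% attrition, power for aflatoxin would fall from about 0.83 to between 0.75 and 0.53. Even the 10% case lies below the planned 0.80.

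**What to change.** In the sampling section, replace geographic proximity with geographic separation between selected clusters, for example no adjoining villages unless they are randomized together as one parish. The rule has to apply to all selected clusters, because arms do not exist at selection. It cannot rest on shared drinking-water sources either: the water-sampling section identifies those through participants, who are recruited after randomization.

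Make the sampling and statistical methods sections say the same thing. If that is what randomizing at the parish level means, state that the parish is the unit of assignment and that clusters in one parish share an arm.

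Recruitment began in March 2021. If the clusters are already fixed, correct the text and report the actual distances between clusters in different arms and any water sources they share.

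The cost is a change of wording and somewhat fewer candidate villages. If the parish is confirmed as the unit, there are also fewer than 60 independently assigned units (at most 56 by Table 1), which the analysis should reflect.
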